#### Placebo control group

Patients are administered dummy *Baoji Tablets* 0.9 g and dummy *Baoji Pills* 3.7 g three times daily for 3 days.

All groups receive health education for the common cold, such as the recommendation to increase rest and fluid intake. During the study, patients are visited four times by the investigators. The time points for the visits are 0.5 days before baseline, at baseline, 4 days post baseline and 11 days post baseline. The follow-up visits last for one week after the treatment. Details of study visits and contents can be found in Figure 2.

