### Outcome measurements

#### Primary outcomes

The primary outcome of this study will be the duration of all symptoms, which is defined as the number of hours from baseline to the time when the patient feels not sick at all. This can be acquired from the patient diary, in which each patient records any changes in symptoms.

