### Sample size calculation and statistical analysis

The sample size was determined using PEMS 3.1 with 90% power and alpha = 0.05 (two-sided). The mean duration of all symptoms for a common cold was estimated to be 7 days with a standard deviation of 4 days [15]. To demonstrate a reduction in the duration of all symptoms by 2 days, which is defined as clinically relevant, the sample size needs to be 85 cases for each group. Considering the potential loss of patients, the number of participants recruited must be 96 per group. Therefore, a total of 288 patients will be recruited in this trial.

The statistical analysis for this study will be performed by an independent professional statistician using PEMS 3.1 in a separate location. An intent-to-treat analysis for the patients, who have received treatment at least once, will be carried out. Missing data will be adjusted using the last observation carried forward method. The per-protocol analysis will be restricted to participants who strictly follow the protocol and complete the study. The safety analysis will be conducted only for randomized subjects who have completed at least one study visit. Pearson’s chi-square test or Fisher’s exact test will be performed on categorical variables, Student’s *t*-test on continuous normally distributed variables and the Wilcoxon rank sum test on non-normal variables. Due to the multicenter design, the Cochran–Mantel–Haenszel test stratified by clinical centers and analysis of covariance adjusted for clinical center and baseline will be used in this study. The statistical significance level will be set at *P* < 0.05 and 95% confidence interval will be calculated.

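### The primary outcome is a time to recovery, but the listed tests and last observation carried forward give no valid value to patients whose recovery is not observed

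*Protocol article*

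**What the plan says.** Under Primary outcomes, the Protocol article defines the duration of all symptoms as "the number of hours from baseline to the time when the patient feels not sick at all". The source is the diary: "This can be acquired from the patient diary, in which each patient records any changes in symptoms". The article does not say when the diary ends.

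The visit schedule, in the last part of Interventions, places the final two visits at "4 days post baseline and 11 days post baseline" and adds: "The follow-up visits last for one week after the treatment".

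Under Sample size calculation and statistical analysis, the mean duration is "estimated to be 7 days with a standard deviation of 4 days" and the target is a reduction of 2 days. The same section assigns the t-test "on continuous normally distributed variables and the Wilcoxon rank sum test on non-normal variables". It also lists analysis of covariance adjusted for centre and baseline, and LOCF for missing data in an intent-to-treat analysis of patients treated at least once. It names no censoring rule and no time-to-event method.

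Under Other criteria, patients who worsen and need hospital treatment are withdrawn, as are those who cannot complete follow-up.

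**The concern.** A time to recovery is known only for patients seen to recover. For someone still ill at the last contact, or withdrawn while ill, the data give a lower bound. The t-test, the Wilcoxon test and analysis of covariance each need one number per patient, so a number must be supplied or the patient left out.

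The only rule stated for this is LOCF, which does not fit the outcome. A symptom score has earlier values to carry forward; a recovery time does not. If LOCF is read as using the last time observed, a patient withdrawn early for worsening enters the analysis with a short illness, so a treatment failure looks like a success.

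The patients affected are those with the longest illnesses, and there are more of them in the slower arm. The handling rule therefore changes the estimated difference, which is the quantity the sample size was built on and which is meant to inform a phase III trial.

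**Working it through.** **Inputs from the article.** Control mean 7 days, SD 4; difference 2 days, so treated mean 5; two-sided alpha 0.05; power 90%; 85 per group; last visit day 11.

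**Assumptions added here.** Observation ends at day 11 (taken from the visit schedule). The 7 days count from baseline (varied in step 4). Treated SD is 4, or 2.86 for the same coefficient of variation (4 × 5/7). Four distribution shapes are used, because the article gives none.

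**1. The plan's own figure.** n = 2 × SD² × (z₀.₉₇₅ + z₀.₉₀)² / difference² = 2 × 16 × (1.960 + 1.282)² / 4 = 84.06, so 85 per group. The stated size reproduces. It is a calculation for two fully observed means.

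**2. Share unrecovered at day 11.** Day 11 is the control mean plus one SD: (11 − 7)/4 = 1. For a normal shape, P(T > 11) = 1 − Φ(1) = 15.9%. The other shapes are matched to the same mean and SD.

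**3. What becomes of a true 2.0-day difference.** Dropped: difference in E[T | T ≤ 11]. Capped: difference in E[min(T, 11)].

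| Shape | Treated SD | Controls past day 11 | Treated past day 11 | Dropped (days) | Capped (days) |
|---|---|---|---|---|---|
| Gamma | 4 | 14.9% | 8.3% | 1.60 | 1.82 |
| Gamma | 2.86 | 14.9% | 3.9% | 1.06 | 1.60 |
| Lognormal | 4 | 13.2% | 7.0% | 1.62 | 1.83 |
| Lognormal | 2.86 | 13.2% | 4.0% | 1.19 | 1.62 |
| Normal | 4 | 15.9% | 6.7% | 1.41 | 1.78 |
| Normal | 2.86 | 15.9% | 1.8% | 0.98 | 1.68 |
| Weibull | 4 | 16.0% | 8.5% | 1.57 | 1.83 |
| Weibull | 2.86 | 16.0% | 3.4% | 0.97 | 1.61 |

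Example (gamma, treated SD 2.86). Recovered-only means are 5.73 and 4.67, a difference of 1.06. Capped means are 0.851 × 5.73 + 0.149 × 11 = 6.52 and 0.961 × 4.67 + 0.039 × 11 = 4.92, a difference of 1.60.

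Dropping gives 1.06-1.62 days for the gamma and lognormal shapes; the normal and Weibull shapes reach just below 1.0.

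**4. If the 7 days run from symptom onset.** Inclusion allows up to 48 hours between onset and presentation. With baseline 1 or 2 days after onset, the control share past day 11 is P(T > 12)/P(T > 1) or P(T > 13)/P(T > 2). Across the normal, gamma and lognormal shapes this is 10.0-11.3% and 7.5-8.7%. For the normal shape with a 2-day lag, the figure is 6.7% without conditioning on still being ill at baseline. The range is about 7-11%; the Weibull shape with a 1-day lag gives 12%.

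**5. Test behaviour with a common day-11 cap and no other loss.** Simulation used 85 per arm, 3,000 runs, and gamma, lognormal and Weibull shapes. Null rejection for the capped t-test and Wilcoxon test was 3.9-6.2%. Power was 94-99% for the capped t-test, 92-99% for the capped Wilcoxon test, and 86-96% for log-rank censored at day 11. Dropping the unrecovered gave an approximate power of 54-99%, depending on shape.

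**The case against.** The strongest reply is that the article is a condensed plan. It lists tests by type of variable and ties none by name to the primary outcome; a separate analysis plan may settle how unrecovered patients enter. That is fair as to silence. It does not rescue LOCF, which is stated as the missing-data rule without exception and cannot work for this outcome.

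A second reply is that the harm may be modest, and much of this stands. A reader might call every figure below 2.0 days a bias. The capped figures are not: with cut-off only at day 11, the difference in capped means is exactly the restricted-mean difference that the fix below offers as a primary contrast. Distortion arises from dropping patients, or from treating a censored time as a recovery. The article does not say that unrecovered patients are dropped, so the dropped figures show what one possible handling would do.

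A third reply is that the day-11 cut-off is inferred from the visit schedule. That also stands. A diary kept until every patient recovered would remove the day-11 part of the problem, though not the early withdrawals. The article states no such provision, and it gives no basis for supposing that the diary stops at day 4 either.

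Two further inferences are not supported. One is that the primary test is wrong because durations are not normal: the article already sends non-normal variables to the Wilcoxon test. The other is that the smallest of several p-values will be chosen: nothing in the text proposes that, and covariance adjustment for baseline fits the symptom scores more naturally than a duration.

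**Conclusion.** The concern holds in a limited form: the stated tests and LOCF have no valid way to enter a patient whose recovery was not observed. On the plan's own mean and SD, about 13-16% of controls and 2-8% of treated patients would be in that position at day 11, plus anyone withdrawn earlier. The control share falls to about 7-11% if the planning mean counts from onset. Leaving these patients out would turn a 2.0-day difference into about 1.1-1.6 days, and slightly less under some shapes.

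These sizes rest on observation ending at day 11, on the assumed shapes, and on a treated SD between 2.86 and 4. A reader might infer that the test is invalid or the trial too small. The calculations do not support that: with capping alone, type I error stays near 5% and power at or above 90%. The issue is how the effect is defined and estimated. It should be fixed, and is not fatal.

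**What to change.** For the primary outcome, replace the t-test, Wilcoxon, analysis of covariance and LOCF wording with one pre-specified time-to-event analysis stratified by centre:

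- Censor at the last diary entry, or at day 11 if not recovered, and show Kaplan-Meier curves by arm.
- Name a single primary contrast: either the difference in restricted mean days sick to day 11, or a centre-stratified log-rank test with a Cox model.
- State that the diary runs to recovery or day 11.
- Because withdrawal for worsening is unlikely to be independent of recovery, add a sensitivity analysis that counts such patients as not recovered through day 11.
- Keep the listed tests for the symptom-score outcomes.

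The cost is mainly wording, with no extra patients. The restricted-mean estimate is days sick up to day 11, so a true 2-day effect would appear as about 1.6-1.8 days, and this should be said in advance. Log-rank alone may fall to about 85% power for some shapes, below the planned 90%. The trial is already recruiting, so the diary instructions in use need to be confirmed; if the diary stops before day 11, data collection changes as well.

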### Randomization and blinding

Stratified blocked randomization is used in this study. Stratification is performed on enrolling centers and block length will be decided by an independent coder, using the software called Package for Encyclopaedia Medical Statistics 3.1 (PEMS 3.1) to generate the randomization sequence. Patients are assigned to the new tablets group, old pills group or placebo control group using a 1:1:1 ratio. The assignment for each patient is concealed in a sealed, lightproof and numbered envelope. Each envelope is assigned to a unique coded test drug package containing the specified medication according to the group assignment. For example, if a patient is assigned to the new tablets group, their unique coded test drug package will contain real *Baoji Tablets* and dummy *Baoji Pills*. Patients are randomly enrolled using the numbered envelopes and assigned to a treatment group. A blinded clinical assistant in each center performs the patient allocation. As the trial is double blinded, both investigators and patients are blinded to group assignments. The sealed envelopes are kept in locked drawers and will only be opened if there is a medical emergency.

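### The rank test listed for non-normal outcomes, probably including the primary duration, leaves out center although randomization is stratified by center; a center-stratified rank test should be fixed in advance

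*Protocol article*

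**What the plan says.** Under Randomization and blinding, the protocol article states: "Stratification is performed on enrolling centers". Patient population and setting fixes four hospitals with 72 patients each, so with 1:1:1 allocation there are 72/3 = 24 patients per arm in each center.

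Sample size calculation and statistical analysis sorts the tests by type of variable: chi-square or Fisher for categorical variables, Student's t-test for normal continuous ones, and "the Wilcoxon rank sum test on non-normal variables". None of these has a center term. The next sentence gives the multicenter design as the reason for adding two adjusted methods: a CMH test stratified by center, and "analysis of covariance adjusted for clinical center and baseline will be used in this study". The article does not say which of these tests decides the primary outcome.

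The primary outcome is the number of hours from baseline until the patient feels entirely well, taken from the diary. The planning assumption is: "The mean duration of all symptoms for a common cold was estimated to be 7 days with a standard deviation of 4 days".

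**The concern.** When randomization is balanced within centers, differences between centers cancel out of the treatment comparison. A test that ignores center still counts that between-center spread as noise. Its true type I error then lies below the nominal level, and it detects less than the same test stratified by center.

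The primary duration probably meets this problem. The rule by variable type sends it to the plain rank-sum test if it is not normal. The two center-adjusted methods do not clearly take over. Analysis of covariance is a linear-model method that adjusts for a baseline value, and a time from baseline to recovery has no baseline value of its own. CMH is named without rank scores, so a reader may take it to apply to the recovery categories. The choice also turns on whether the variable is normal, which can be settled only by looking at the trial's data. At stake are some efficiency and a clear, pre-specified primary test. There is no added risk of a false positive.

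**Working it through.** **1. The plan's own sample size.** Inputs, all from the sample size section: two-sided alpha 0.05, power 90%, SD 4 days, difference 2 days. n = 2 × (1.960 + 1.282)² × 4² / 2² = 2 × 10.51 × 4 = 84.06, rounded up to 85. This matches "the sample size needs to be 85 cases for each group". Under the same formula, power is 90.3% at 85 and 93.4% at 96 per group. The calculation uses the total SD and no center adjustment.

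**2. Is the duration likely to be non-normal?** Under a normal model with SD 4, the share below zero is Φ(−7/4) = Φ(−1.75) = 4.0% at mean 7, and Φ(−5/4) = Φ(−1.25) = 10.6% at mean 5 (7 minus the planned 2). A duration cannot be negative, so some right skew is likely. The article does not say so; this is inferred from its figures.

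**3. Why the test becomes conservative.** Let ρ be the share of total variance that lies between centers. With arms balanced within center, the true variance of the comparison is about (1 − ρ) times what an unstratified test assumes. For a test on means, the true error is therefore about 2 × [1 − Φ(1.960/√(1 − ρ))]:

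- ρ = 2%: 1.960/0.990 = 1.980, error 4.8%
- ρ = 5%: 1.960/0.975 = 2.011, error 4.4%
- ρ = 10%: 1.960/0.949 = 2.066, error 3.9%
- ρ = 20%: 1.960/0.894 = 2.191, error 2.8%

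**4. Simulation for the rank test.** Four centers, 24 per arm per center (96 per arm), mean 7, total SD 4, 20,000 trials per setting. The plain rank-sum test was compared with the van Elteren test. The values of ρ are assumptions, because the article gives none.

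Type I error of the plain test:

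| ρ | Skewed (gamma), fixed center effects | Normal, fixed center effects | Skewed (gamma), random center effects |
|---|---|---|---|
| 0% | 5.1% | 4.8% | not tabulated |
| 1% | 4.7% | 4.9% | not tabulated |
| 2% | 4.8% | 4.9% | not tabulated |
| 5% | 4.0% | 4.2% | 4.5% |
| 10% | 3.7% | 4.0% | 3.8% |
| 20% | 2.6% | 3.0% | 3.4% |

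The stratified test stayed between 4.6% and 5.3% throughout. Repeat runs with random center effects gave up to 4.8% at ρ = 5%, so about 4–5% is a fair range there. The simulation error on one 5% entry is √(0.05 × 0.95/20,000) = 0.15 points.

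Power, plain against stratified, 96 per arm:

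| ρ | 2 days, gamma | 2 days, normal | 1.5 days, gamma |
|---|---|---|---|
| 0% | 98.7 vs 98.6 | 92.1 vs 91.6 | 82.1 vs 81.4 |
| 5% | 98.5 vs 98.8 | 92.4 vs 92.6 | 81.8 vs 83.1 |
| 10% | 98.5 vs 99.2 | 93.2 vs 94.1 | 81.7 vs 84.8 |
| 20% | 98.2 vs 99.6 | 94.0 vs 96.2 | 82.4 vs 88.7 |

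At the planned 2 days, stratifying gains about 0 to 2 points. With 84 per arm (21 per arm per center, close to the planned evaluable number), it gains 0.4–0.8 points at ρ = 5%, about 1.5 at 10% and 2.6–3.3 at 20%. At 1.5 days and 96 per arm, the gain is 1.3, 3.1 and 6.3 points. With no center effect, stratifying costs 0.1 to 0.7 points.

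**The case against.** The strongest reply is that the plan already handles center. The sentence after the list of simple tests adds a center-stratified CMH test and a center-adjusted analysis of covariance, and it limits neither to a type of outcome. CMH applied to ranks is the stratified rank test. A reader might infer that the plan ignores the factor it stratifies on; the text does not support that. It is also fair that matching each test to an outcome is often left to an analysis plan, and that plan is not shown here. What remains is that the one rank test this article assigns to non-normal variables has no center term, and nothing in the article replaces it for the primary duration.

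Second, a reader might take it as settled that the error rate falls below 5% and power is lost. The documents do not support this either. It depends on centers differing, and no between-center variance is given. The Discussion requires all centers to follow the same standard operating procedures, which may keep differences small. At shares of 2% or less the effect cannot be told apart from simulation error.

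Third, a reader might infer that the promised 90% power is missed. At 96 per arm and the effect the plan calls relevant ("To demonstrate a reduction in the duration of all symptoms by 2 days, which is defined as clinically relevant"), plain rank-test power stayed above 90% in every setting tried. It hardly moves as center variance grows; the gap opens because the stratified test gains. With 84 per arm and normal data, plain power dips to about 88% even without center effects. That is the rank test's cost on normal data, not a center problem. The larger gaps belong to a 1.5-day effect, which the plan does not use.

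Finally, the error is on the conservative side, so a positive result would not be in doubt.

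**Conclusion.** The point holds as a modest improvement. As written, a non-normal outcome goes to a rank test without center, the primary duration is probably such an outcome, and neither adjusted method is assigned to it. If centers differ, that test runs at about 4–5%, 3.7–4% and about 3% true error for between-center shares of 5%, 10% and 20%. At 2 days and 96 per arm it forgoes about 0–2 points of power. At 1.5 days it forgoes about 1–6 points over the same shares. With shares of 2% or less nothing material changes. These sizes rest on assumed center shares, on balanced arms within each center, and on gamma or normal durations with SD 4. The validity of a positive finding is not threatened.

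**What to change.** In Sample size calculation and statistical analysis, replace the plain Wilcoxon test for the primary duration and the other non-normal outcomes with its center-stratified form: the van Elteren test, which is the CMH test already named, applied to ranks within center. Name it in advance as the primary test, so that no normality check on the trial data decides. If another method for durations is adopted, stratify it by center too.

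The cost is one sentence, plus up to about 1 point of power if centers do not differ at all. The article reports that recruitment is still under way, so the change can be made before the blind review of the data.

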## Discussion

To date, there are still no effective therapeutic options available to treat the common cold. It seems that a vaccine may be a good solution. However, vaccines only work on certain viruses. Besides, since diverse viral serotypes cause the common cold, vaccine preparation is very difficult. Therefore, recent studies have mainly focused on symptomatic management. TCM is widely used in China to treat the common cold and many studies have shown that a TCM formulation might be better in reducing symptoms than a placebo [16-19]. However, the quality of many of these reported studies is of great concern [20]. A number of high-quality clinical trials are needed before any Chinese herbal preparation can be recommended for the common cold [21]. For this reason, the study protocol was designed according to the Consolidated Standards of Reporting Trials statement [22]. Quality controllers will pay regular visits to each center, recheck CRFs and monitor the research data throughout the trial. Moreover, investigators in different centers are all required to follow the standard operating procedures. To our knowledge, previous studies have only focused on wind-cold syndrome and wind-heat syndrome. Therefore, this will be the first multicenter, double-blind, double-dummy, randomized and placebo-controlled trial designed to treat CCSDS in an adult population from China. It will establish the basis for a scientific and objective assessment of the efficacy and safety of *Baoji Tablets* for treating CCSDS, and provide evidence for a phase III clinical trial.

## Trial status

This trial is currently recruiting participants.

## Abbreviations

CCSDS: common cold with summer-heat and dampness syndrome; CFDA: China food and drug administration; CRF: case report form; PEMS: Package for encyclopaedia medical statistics; PSSR: percentage of symptom score reduction; TCM: traditional Chinese medicine.
